## Abstract

**Background:**

The COVID-19 pandemic has a lasting impact on health care utilization, as both the acute infection and post COVID condition (PCC) can lead to increased demand for medical services due to ongoing symptoms.

**Objective:**

The aim of this study is to systematically examine health care utilization among individuals after acute SARS-CoV-2 infection in Bavaria, Germany, with a particular focus on PCC. The study combines claims data analysis with qualitative interviews to improve the understanding of objective care pathways and patients’ subjective experiences within the health care system.

**Methods:**

The research project ‘SOLongCOVID’ employs a mixed-methods design consisting of two subprojects: (1) a retrospective cohort study using claims data from the Bavarian Association of Statutory Health Insurance Physicians (KVB) to analyze care pathways through state sequence analysis, (2) a qualitative study based on semistructured interviews and focus groups with patients with PCC concerning their subjective care experiences. A synthesis process involving a focus group discussion will combine the information from the two subprojects, providing a comprehensive understanding of the care processes of patients with PCC.

**Results:**

The study was funded by the German Federal Joint Committee Innovation Fund in October 2024. Statutory health insurance claims data cover the period from 2019 to 2022, and qualitative interview data collection is planned from May 2025 to August 2026. As of manuscript submission, study preparation and ethics approvals have been completed, and 14 participants have been recruited for the qualitative interviews. Study findings are anticipated to be published from July 2026 to August 2027.

**Conclusions:**

The results are expected to enhance the understanding of existing barriers and challenges and to support evidence-based recommendations for improving care pathways for patients with specific care needs.

## Introduction

According to the World Health Organization, more than 770 million people worldwide have been infected with Severe Acute Respiratory Syndrome Coronavirus 2 (SARS-CoV-2), with approximately 6.9 million deaths [1]. While symptoms often subside within 14 days, many patients continue to have symptoms after the acute illness [2,3]. The generally used term ‘long COVID,’ medically described as *post-COVID-19 condition* (PCC) is defined as the presence of symptoms that persist or newly develop three months after a SARS-CoV-2 infection and last for at least two months without an alternative explanation [4]. The symptoms experienced by patients with PCC are highly diverse and reflect the multifaceted nature of the condition. These symptoms can affect multiple systems of the body, further highlighting the complexity of the condition [3,5,6]. However, there are certain symptoms that occur more frequently. These include fatigue, myalgia, neurological symptoms such as cognitive impairment, loss of smell and taste, as well as headaches, mental health issues, including depression and anxiety, and cardiopulmonary symptoms like dyspnea, chest pain, and palpitations [5,7-11].

The broad range and duration of these symptoms, combined with the diverse nature and unpredictability of PCC, often lead to increased and prolonged health care utilization in both ambulatory and hospital settings, as demonstrated in several studies [12-15]. The increase in utilization has a major impact on the health care system, which is faced with rising costs and increasing demand for specialized treatment [14,16,17]. A study from the United States showed that SARS-CoV-2 infection was associated with an overall 4% increase in health care utilization within six months of infection, primarily driven by virtual contacts and emergency department visits [18]. Specifically for the ambulatory setting, recent studies on PCC health care utilization have mainly focused on treatment by specialists or consultation with primary care physicians. However, many of these studies are limited by follow-up periods of less than six months [5,8,10,11]. At the same time, international research is increasingly addressing potential barriers to care and patient experiences in accessing PCC-related health care services. These studies indicate that access to care is often limited by long waiting times, a shortage of specialists, and a lack of specialized treatment services. They also underscore the urgent need for patient-centered approaches to improve care for those affected [19-23].

Evidence on long-term health care utilization, particularly with respect to different types of physician services, remains limited. Gaining a more comprehensive understanding of health care utilization and the specific needs of patients following a SARS-CoV-2 infection is essential for policymaking and clinical management of affected patients.

To improve the understanding of both objective care pathways and subjective patient experiences, claims data derived from the routine records of the Bavarian Association of Statutory Health Insurance Physicians (KVB) will be analyzed, and qualitative interviews and a focus group will be conducted to examine the individual care experiences of people affected by PCC. The aim of the study is to systematically examine health care utilization among patients after an acute SARS-CoV-2 infection, in Bavaria, Germany, with a particular focus on PCC. The study combines claims data analysis with qualitative interviews to improve the understanding of objective care pathways and patients’ subjective experiences within the health care system.

## Methods

To ensure a high scientific standard and transparency, the reporting of this study protocol and the study results will adhere to the following guidelines: the *Strengthening the Reporting of Observational Studies in Epidemiology* (STROBE) guideline and the *Consolidated criteria for reporting qualitative research* (COREQ) Checklist [24-26]. The study is registered in the German Clinical Trials Register (registration number DRKS00038446).

### Ethical Considerations

The claims data analysis and the qualitative study were approved by the Local Research Ethics Committee of Ludwig-Maximilians-University Munich (reference number 25‐0173-KB and 25‐0276). Written informed consent is obtained from each participant after they had been informed about the study’s aims, procedures, voluntary nature, and data protection measures. Participant privacy and confidentiality are strictly maintained throughout the study. Personal identifiers are removed or not collected where not essential, and all data are handled and stored securely in accordance with institutional ethics and data protection guidelines. No identifiable personal information is reported in this manuscript. Copies of the signed consent forms are securely stored in accordance with institutional ethics guidelines. No compensation is provided to participants.

### Study Design

The study follows a convergent mixed-methods design aiming to describe and analyze the trajectories of patients following an acute SARS-CoV-2 infection in the ambulatory setting (see Figure 1). Quantitative analyses of statutory health insurance claims data and qualitative interview analyses will be conducted in parallel and independently. Data and results from two subprojects will be used to facilitate the synthesis.

**Figure 1. F1:**
[figure not shown]
Mixed-methods study approach.

First, in a retrospective cohort study with claims data (Subproject 1) objective care pathways will be reconstructed based on routine data from the KVB. To do so, three cohorts will be defined, a cohort of patients with SARS-CoV-2 infection and a cohort of patients with other respiratory tract infection during the pandemic phase 2020 till 2022. To measure the impact that the pandemic had on the overall health care utilization, we will also form a historic control group with respiratory tract infections in the year 2019.

Second, a qualitative study (Subproject 2) will be conducted, including semistructured interviews with people affected by PCC concerning their individual subjective experiences and personal motivations for (non-) utilization of care.

The integration of the results will take place at the interpretation stage through systematic triangulation. Quantitatively identified care pathways will be compared with themes derived from patient interviews to identify areas of convergence, complementarity, and divergence. Joint displays will be developed that compare quantitative care trajectories with qualitative interview data, enabling structured comparisons across data sources. This will be achieved by using the software MAXQDA (version 24.9.1), as referenced by Kuckartz [27,28].

All results will be synthesized in a focus group in order to record and understand the care processes holistically and to classify them in the light of the existing evidence. The focus group will serve to validate and refine the results of the individual interviews, to contrast individual experiences within a group setting, and to enable in-depth exploration of shared experiences and interpretive patterns. Moreover, it supports the development of evidence-informed recommendations for care improvement. The synthesis will be published in scientific journals and made accessible to affected individuals and care providers to ensure broad dissemination and practical impact.

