### Participants and Data Collection

The subprojects will be informed by a systematic literature review performed before the project (manuscript forthcoming).

*Subproject 1:* KVB claims data will be used for the analysis. The KVB data includes all claims for ambulatory physicians in the State of Bavaria made by insured persons residing in Bavaria. The analysis is based on the *Bavarian COVID-19 Cohort* which was established from anonymized billing records of all patients with statutory health insurance in Bavaria. Both general practitioners and medical specialists submit details on patient encounters, including treatments, diagnoses, and billing information, to the KVB in each quarter. The dataset includes pseudonymized patient identifiers, demographic variables (age, sex, region), diagnoses (International Classification of Diseases, 10th Revision, ICD-10 codes with diagnostic certainty) and billed services (EBM codes, specialty, and practice identifiers). This structure allows longitudinal tracking of health care utilization, comorbidities, and treatment patterns across cohorts.

Out of 9,202,930 individuals with any respiratory infection, 4,247,455 had a confirmed COVID-19 diagnosis and the remained any other respiratory infection. For the analysis, three cohorts were randomly drawn:

COVID-19 (2020–2022): 196, 000 individuals with a confirmed diagnosis of COVID-19, ie, *ICD* codes U07.1 or U08.9 or U09.9 (secured and suspected diagnoses)Control (2020–2022): 140,000 individuals matched to the COVID-19 cohort by age and sex who received a confirmed ambulatory diagnosis of a respiratory infection (*ICD* J00*–J22*, J40*–J42*) in the same quarter.Historical control (2019): 140,000 individuals with a confirmed respiratory infection (*ICD* J00*–J22*, J40*–J42*) diagnosed in 2019, matched by age and sex to the COVID-19 cohort

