*Subproject 2:* Patients with PCC will be asked to participate in individual interviews about their experiences with health care delivery. Inclusion criteria comprise adult patients from the Munich region and the wider Bavaria area who either have a confirmed diagnosis of PCC or self-report having experienced PCC in the past or currently. Participants must have received or be receiving ambulatory treatment. Recruitment will be conducted through PCC support groups in Munich. These groups bring together individuals affected by PCC who meet regularly to exchange experiences and provide mutual support. A semistructured interview guideline will be developed and tested, taking into account individual experiences and care processes. Findings from the systematic review will be incorporated into the development of the guidelines. The guideline will establish a thematic framing and consists of all relevant topics that need to be addressed in the interview. It ensures better comparability of the data and structures the entire communication process [29]. Potential interview partners for the qualitative part of the project will be recruited utilizing a snowball sampling approach wherever possible [30]. This process follows the principle of maximum variation, aiming to capture a diverse range of perspectives and experiences. The qualitative interviews and the focus group will be conducted in person or via video conference. During the interview, patient journey maps will be developed [31,32]. The number of interviews is determined according to the methodological criterion of theoretical saturation [33]. The sample is expected to consist of around 20 to 25 participants. Should saturation be achieved earlier, indicated by the emergence of no new themes, a reduced number of interviews will be conducted. Conversely, if saturation is not attained, the sample size will be stepwise increased until the required number is reached.

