### Data Analysis

#### Subproject 1

For the claims data, control groups will be matched by age, gender, and time of diagnosis (year/quarter). We will analyze the utilization patterns longitudinally for the cohorts and will focus specifically on the health care service billing group. We will estimate the incidence of PCC diagnoses (*ICD* codes: U09.9, U07.4), as well as newly occurring comorbidities, which may also be in the context of PCC. Expected outcomes are: (1) SARS-CoV-2 related symptoms, (2) newly developed diseases (cardiovascular diseases, autoimmune diseases, mental health diseases). Here, a special focus will be on diseases related to PCC, irrespective of a specific PCC diagnosis (eg, ICD-10 codes: R53, G93.3, F06.7, R43, M79.1, I26, R05, F48.0, F41) [4,34]. Health care utilization is analyzed using a *State Sequence Analysis* (SSA) [35]. Analyses are conducted for the cohort of SARS-CoV-2 infections and the control groups. In the analysis, the health care utilization for primary and specialist care as well as their respective diagnoses will be analyzed in the time before and after the SARS-CoV-2 infection. A specific focus will be on the appearance of a PCC diagnosis or diagnoses of PCC-related conditions. SSA identifies individual care trajectories represented as ordered sequences of quarterly states, where each state reflects contacts with general practitioners, COVID-19 specialists, or other specialists. Dissimilarities between trajectories are quantified using a theory-driven cost matrix, and clusters of patients with similar utilization patterns are derived through an unsupervised medoid-based clustering procedure. The optimal number of clusters is selected based on established quality indices (eg, average silhouette width). Factors associated with the resulting care pathway clusters are subsequently analyzed using multivariable regression models.

Additionally, the potential health care utilization depends on regional factors. Therefore, the place of residence of the cohort is recorded at the level of the districts and independent cities of Bavaria as well as the degree of urbanization of the municipality of residence. The regional distributions of the cohort and utilization patterns are visualized and analyzed using *geographical information systems* (GIS). Differences are analyzed using hierarchical regression models.

#### Subproject 2

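### Claims pathways come from all infected patients and controls, but are set against interviews with PCC patients only, so divergence may be confounded with a difference in population

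*Protocol article*

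**What the plan says.** **Claims side.** On the sequence analysis, Data Analysis (Subproject 1) says: "Analyses are conducted for the cohort of SARS-CoV-2 infections and the control groups". Trajectories are built from quarterly states, where "each state reflects contacts with general practitioners, COVID-19 specialists, or other specialists". Then "clusters of patients with similar utilization patterns are derived through an unsupervised medoid-based clustering procedure", and quality indices such as average silhouette width decide the number of clusters. The same section plans to estimate the incidence of PCC codes (U09.9, U07.4), promises particular attention to the appearance of PCC or PCC-related diagnoses, and relates unspecified factors to cluster membership by regression.

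Participants and Data Collection gives the cohorts:
- "196, 000 individuals with a confirmed diagnosis of COVID-19", with U07.1, U08.9 or U09.9 as entry codes;
- a concurrent control of "140,000 individuals matched to the COVID-19 cohort by age and sex";
- a historical control of 140,000 from 2019.

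**Interview side.** Those eligible are "adult patients from the Munich region and the wider Bavaria area who either have a confirmed diagnosis of PCC or self-report having experienced PCC", and they must have had ambulatory treatment. The focus group is drawn from the interviewees.

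**Integration.** Study Design (text below Figure 1) says: "Quantitatively identified care pathways will be compared with themes derived from patient interviews to identify areas of convergence, complementarity, and divergence". Data Analysis (Subproject 2) adds that the claims pathways are shown to the focus group, that aspects of care where the two sources disagree are identified, and that the group develops recommendations.

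**Target.** The Methods part of the Abstract describes the synthesis as "providing a comprehensive understanding of the care processes of patients with PCC". The Discussion likewise speaks of the objective pathways of patients with PCC. Study Design opens with a wider target: trajectories after acute infection.

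**The concern.** The claims arm follows the wider target, while the interviews and the synthesis follow the PCC target. The two sides therefore differ in data source (recorded contacts against reported experience) and also in population (anyone with a COVID-19 code, plus controls, against people with PCC). The plan reads a divergence as a difference of the first kind. As written, the second kind could produce it as well.

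Suppose the claims clusters show mostly general-practice contact while the interviews describe long searches among specialists. That pattern could arise even if claims and interviews agreed completely for patients with PCC. Recommendations are then developed in a focus group that has been shown those pathways. The limitations in the Discussion cover support-group selection and region, but not this difference.

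**Working it through.** The article states no figure to reproduce. The check sets the populations side by side and then asks how far a whole-cohort pathway distribution can stand in for that of PCC patients.

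**1. Populations as stated**

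| Step | Population | Section |
|---|---|---|
| Sequence analysis and clustering | SARS-CoV-2 cohort and control groups | Data Analysis, Subproject 1 |
| Interviews | Confirmed or self-reported PCC | Participants and Data Collection |
| Focus group | Drawn from the interviewees | Participants and Data Collection |
| Joint displays | Claims pathways (no subset named) against interview themes | Study Design |
| Synthesis target | Patients with PCC | Abstract, Discussion |

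PCC status is not a state in the sequences, because states are provider contacts. No stratification of the clustering by PCC is stated.

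**2. Cohort sizes**

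196,000 + 140,000 + 140,000 = 476,000. The COVID-19 cohort is 196,000 / 476,000 = 41.2% of the total; the controls are 280,000 / 476,000 = 58.8%.

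**3. Number of PCC patients under assumed shares**

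The PCC share p of the COVID-19 cohort is not in the article; its incidence is one of the planned estimates. The range below is an assumption. The last column applies only if all three cohorts are clustered together, which the article does not say.

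| Assumed p | PCC patients = p × 196,000 | Share of 476,000 |
|---|---|---|
| 1% | 1,960 | 0.4% |
| 5% | 9,800 | 2.1% |
| 10% | 19,600 | 4.1% |
| 20% | 39,200 | 8.2% |
| 30% | 58,800 | 12.4% |

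PCC patients are a minority of the COVID-19 cohort whenever p < 50%. In a pooled clustering they could be at most 41.2%.

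**4. What this does to a comparison**

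For a given pathway type, let a be its frequency among PCC patients and b its frequency among the rest of the COVID-19 cohort. The cohort frequency is p·a + (1 − p)·b. The gap between PCC patients and the cohort is

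a − [p·a + (1 − p)·b] = (1 − p)(a − b).

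This gap exists with no disagreement between claims and experience. At p = 5% it is 95% of the true difference between PCC and other patients; at p = 30% it is 70%. If a = b it is zero. The article gives neither a nor b, so the size of the gap is unknown.

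**5. Whether regression on clusters would repair it**

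Suppose PCC status were a covariate and identified a PCC-rich cluster. At an assumed p of 5% and four-fold enrichment, the cluster would hold 4 × 5% = 20% PCC patients and 80% others. Its medoid need not be a PCC pathway.

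**The case against.** The strongest reply is that a journal article condenses the full plan, and that the choice of trajectories for a joint display may be settled there. The attention to PCC diagnoses sits inside the description of the sequence analysis, the study aim has a particular focus on PCC, and PCC patients are inside the clustered cohort because U09.9 is an entry code. Nothing excludes PCC-specific trajectories. Integration is interpretive, no test depends on matched populations, and focus-group members can say which pathways resemble their own care.

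Part of this stands. A reader might infer that convergence and divergence will largely reflect two different populations, or that the clusters must describe ordinary use after infection. The documents do not support either inference. They give no PCC share, do not say whether the cohorts are clustered together, and do not show how far PCC patients differ in utilization. A range restricted to coded PCC would also leave out patients with PCC-related diagnoses, whom the article explicitly wants to study whether or not PCC is coded.

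The rest does not remove the point. The article does more than leave a detail open: it names both populations, the comparison between them and a PCC target. Attention to when a diagnosis appears does not define a set of PCC sequences, and an association with cluster membership is not a PCC pathway. Focus-group recognition may help interpretation, but it cannot separate case mix from a real gap between records and experience.

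**Conclusion.** The concern holds in limited form. As described, the integration compares pathways of all infected patients and controls with the experience of PCC patients, so a divergence may be confounded with a population difference. Agreement may likewise be hard to interpret.

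The size cannot be fixed from the article. It depends on the PCC share, on how much PCC patients' utilization differs from that of the others, and on whether cohorts are pooled. What can be said without assumption is that PCC-coded patients are a minority of the COVID-19 cohort at any share below 50%. The illustrative counts rest on an assumed range of 1% to 30%.

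The claims comparison between cohorts is unaffected; only the synthesis is. The change is worth making before pathways are shown to the focus group.

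**What to change.** 1. In Data Analysis (Subproject 1), add a sequence analysis and clustering in COVID-19 cohort members with a PCC code (U09.9 or U07.4, as listed there). Add a second version in those with a new diagnosis from the section's list of PCC-related codes.
2. State how the index quarter is set for patients who enter on U09.9 without a recorded acute infection.
3. In Study Design and Data Analysis (Subproject 2), name these subgroup pathways as the main claims input to the joint displays and the focus group. Show whole-cohort and control pathways beside them as labelled context, and keep them for the utilization comparison.
4. Add to the limitations that interviewees with self-reported but uncoded PCC still have no matched group in the claims data.

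**Cost.** An additional clustering run for each version on data already held, and a few sentences. The Results section has claims analyses continuing until April 2027 and first interview and focus-group results in August 2026, so the choice should be fixed before the focus group meets. The subgroups are smaller and rely on coding that the Discussion already calls inaccurate. The second version reduces the dependence on a PCC code, but will include patients whose diagnosis has another cause.
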